### Data management and analysis

All data recorded in the eCRF will be stored in a REDCap platform hosted in a local server. The REDCap data will be transferred to a database, which will also contain the data extracted from the local EHR and the CHSS registries. All registries will be linked through the identification number of the Catalan Health Service.

Data recorded in the eCRF will be monitored for completeness and quality by a professional monitor working at the research office of the Hospital acting as sponsor. We will schedule periodic visits to assess the adherence of investigators to the study protocol and good clinical practices. The clinical monitor will release reports at the end of each visit.

A statistical analysis plan, with detailed analyses for each study outcome, will be performed after the last patient has attended the final visit and before the closure of the database.

The primary objective will be assessed using a non-inferiority analysis of the cumulative incidence of complications of the baseline disease between remote consultation (video and teleconsultation arms) and face-to-face consultation, using a non-inferiority margin of 2%. The analysis will be based on a modified binomial test to assess the non-inferiority of an experimental intervention vs. a control group in a three-arm trial [23]. The primary analysis will be conducted on a per-protocol study sample, which will include all participants who have finished the study and have not been withdrawn because of non-allowed visits using modalities other than scheduled. The intention-to-treat population, used for sensitivity analyses, will consist of all randomized patients completing at least one visit. Since the analysis will be based on an event rate, missing data will not be imputed.

The primary analysis will be replicated with patients stratified according to the following characteristics: hospital department, diagnostic, disease duration (chronic vs. acute or sub-acute), anatomic-therapeutic treatment groups, and GMA health risk group. The clinical and demographic characteristics of study participants will be described and compared between excluded/withdrawn participants.

The statisticians will be blinded for the allocation arm. The type I error will be set at 2.5% for the primary analysis and 5% for the rest of the analyses. All analyses will be conducted using R software (version 4.0 or higher) [24]. Data collected during the ECASeT trial will not be re-used.

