### Outcomes and variables

Table 1 summarizes the definitions and data sources of primary and secondary outcomes assessed in this trial. Complications and adverse reactions will be considered only if related to the baseline disease (i.e., the health condition for which the first study visit was scheduled). To prevent interference with routine practice, the investigator will have the option of recording the reference disease in a free-text field in the eCRF. The option of completing a field in English or Spanish linked to the ontologies of the ICD10 will also be available. If this field is not filled in, the ICD-10 code will be extracted from the free-text field. The investigator will also record the stage (if applicable) of the baseline disease and its severity.

**Table 1 Tab1:** Study outcomes and data sources

**Item**	**Domain definition**	**Measure and metrics**	**Data sources**^**a**^

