The follow-up period planned by the investigator for the baseline disease will be retrieved from the local EHR. Other variables collected from EHRs at baseline will include sex, age, area of residence, the number of active prescriptions at the end of the screening visit, and the comorbidity burden, summarized using the Adjusted Morbidity Groups (AMG). Briefly, the AMG is a case-mix tool that generates a summary index of health risk by considering all chronic conditions and recent acute diagnostic codes [17]. The tool allows stratifying patients into mutually exclusive health-risk groups and has shown a high predictive capacity of healthcare and resource use outcomes, including mortality, hospitalization, visits to primary care, polypharmacy, and overall expenditure [18, 19].

For homogeneity regarding the rate of preventable hospitalizations, we considered all hospitalizations due to any of the ICD-10 diagnostic codes listed as ambulatory care sensitive conditions [20] managed in the participating departments, including conditions related to ischemic heart disease (I20, I240, I248, I249), asthma (J45, J46), chronic obstructive pulmonary disease (COPD) (J20, J41, J42, J43, J44, J47), heart failure (I110, I50, J81), seizures (G40, G41, R56, O15), diabetes (E100-E108, E110-E118, E120-E128, E130-E138, E140-E148), high blood pressure (I10, I119), and iron-deficiency anemia (D501, D508, D509).

Usability will be assessed by passive and active surveillance. Study investigators will record non-attendances, as well as all technical incidences that occurred during the visit in an unstructured field of the eCRF. For active surveillance, a trained interview panel will contact by phone a subset of 100 participants randomly selected from all patients who have completed the final visit. Interviewers will administer the computer system usability questionnaire (CSUQ), a validated questionnaire aimed at measuring the users’ satisfaction with the usability of computer systems in scenario-based usability studies [21].

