### Sample size considerations

The sample size was estimated based on the primary endpoint of cumulative incidence of complications related to the baseline disease. The sample size analysis was computed with R software [24], following the approach described by Steen A. Julious for non-inferiority trials [25]. Although there is little available information regarding this outcome in the general population of chronic patients, we expect 10% of events in face-to-face consultations [26–28] and 12% in the remote consultation arm (based on routine practice of the research team). Assuming a type-I error of up to 2.5% and a statistical power of 80%, 1068 subjects per arm should be analyzed to reject the non-inferiority hypothesis with a non-inferiority margin of 2% and assuming 10% of participants lost to follow-up.

Altogether, the participating centers schedule 252,000 routine follow-up visits during a period equivalent to the study, corresponding to 121,400 different patients. Therefore, the recruitment of the estimated 2136 patients is considered within the capabilities of the participating centers.

Owing to the scarcity and heterogeneity of available data about the primary endpoint, a blinded interim analysis will be conducted when 50% of the total sample has been recruited to revise the assumptions used to calculate the sample size, as proposed in the E9 Guide of the ICH on Statistical Principles for Clinical Trials [29].

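### The primary non-inferiority test is unadjusted although baseline risk measures are already retrieved; a prespecified covariate-adjusted risk difference would gain modest precision at almost no cost

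*Protocol article*

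**What the plan says.** All references are to the protocol article.

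- **Primary test** (Data management and analysis): "The analysis will be based on a modified binomial test to assess the non-inferiority of an experimental intervention vs. a control group". The cited method is described as one for trials with three arms. The margin is 2%, and no covariate is named. On error rates: "The type I error will be set at 2.5% for the primary analysis and 5% for the rest of the analyses".
- **Analysis sets** (same section): the per-protocol sample is primary. The intention-to-treat population is used for sensitivity analyses.
- **Use of baseline risk** (same section): the primary analysis is repeated within strata of department, diagnosis, disease duration, treatment group and AMG risk group (there written GMA). Excluded and withdrawn participants are also described and compared.
- **What is collected** (Outcomes and variables): age, active prescriptions at the end of the screening visit, and AMG all come from the health records. Of AMG the protocol says that it "has shown a high predictive capacity of healthcare and resource use outcomes, including mortality, hospitalization, visits to primary care, polypharmacy, and overall expenditure". For the eCRF: "The investigator will also record the stage (if applicable) of the baseline disease and its severity".
- **Timing** (Data management and analysis): the statistical analysis plan is to be produced after the last participant's final visit and before database closure.

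**The concern.** A non-inferiority trial with a 2-point margin on a 10% event rate needs all the precision it can get. A baseline variable that predicts the outcome reduces the variance of the marginal risk difference without one more participant. The plan holds such candidates but leaves them out of the estimate that decides non-inferiority. Results by AMG stratum show whether the difference varies with risk. They do not yield one adjusted overall difference with its own confidence limit.

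Timing matters too. If covariates are first chosen in an analysis plan written after follow-up has ended, the choice is open to question even with blinded statisticians. A choice made by amendment while the trial is recruiting is not.

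The per-protocol primary set adds a smaller reason. After exclusions the groups are no longer exactly as randomised, and an unadjusted estimate carries any resulting imbalance in measured baseline risk.

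This point is about patient-level risk. The medical specialty factor used to balance randomisation is a separate matter.

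**Working it through.** **Inputs from the protocol article.** Control risk: "we expect 10% of events in face-to-face consultations". Remote risk 12%, margin 2 points, loss to follow-up 10%. Size: "Assuming a type-I error of up to 2.5% and a statistical power of 80%, 1068 subjects per arm should be analyzed".

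**1. The plan's own figure.** With pooled variance, n = 2 × 0.11 × 0.89 × (1.960 + 0.842)² / 0.04² = 960.5, so 961 per arm, and 961/0.9 = 1068. Unpooled variance gives 960, and 1067 after loss. The figure reproduces, but only with a denominator of 0.02 + 0.02, which treats the 12% remote risk as better than control. That is a separate and larger problem. It is noted here because 961 per arm is the analysed size used below.

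**2. Precision without adjustment.** At 10% in both arms, SE = √(2 × 0.10 × 0.90 / 961) = 1.369 points. The 95% half-width is 1.960 × 1.369 = 2.68 points. Power at a true difference of zero is Φ(2/1.369 − 1.960) = 30.9%.

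**3. Precision with adjustment.** Adjustment multiplies the variance by about 1 − R², where R² = Var(p)/[p(1 − p)] and p is the risk predicted from baseline. The protocol gives no R². Assume a normal linear predictor in a logistic model with mean risk 10%, and vary the c-statistic. The last column is 2136 × [1/(1 − R²) − 1].

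| c (assumed) | R² | SE (points) | 95% half-width | Power at zero difference | Equivalent extra participants |
|---|---|---|---|---|---|
| 0.60 | 1.2% | 1.36 | 2.67 | 31.2% | about 26 |
| 0.65 | 2.8% | 1.35 | 2.64 | 31.7% | about 62 |
| 0.70 | 5.4% | 1.33 | 2.61 | 32.4% | about 122 |
| 0.75 | 9.2% | 1.30 | 2.56 | 33.5% | about 217 |
| 0.80 | 14.6% | 1.26 | 2.48 | 35.3% | about 366 |

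A cruder check uses two risk strata averaging 10%, with R² = f(1 − f)(p_high − p_low)²/[p(1 − p)]. With 25% of patients at 19% and the rest at 7%, R² = 0.25 × 0.75 × 0.12²/0.09 = 3%. With 20% at 30% and the rest at 5%, R² = 0.20 × 0.80 × 0.25²/0.09 = 11%.

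At the protocol's own 10% versus 12%, the true difference equals the margin, so power is 2.5% whatever is adjusted.

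**4. What adjustment does for exclusions.** Assume control strata of 7% and 19% (25% high risk), a true excess of 2 points in each stratum, and 5-15% of the remote arm excluded with none from control.

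- *Exclusion depends on baseline risk only*, 2-3 times likelier in the high-risk stratum. At 15% and 3 times, 30% of high-risk and 10% of low-risk patients leave. The high-risk share becomes 0.25 × 0.70/0.85 = 20.6%, the remote risk 0.206 × 21% + 0.794 × 9% = 11.5%, and the crude difference 1.5 points. Over the range, the crude difference is 1.9 to 1.5 points. Adjustment for the stratum restores 2.0.
- *Exclusion depends on the event itself*, 2-3 times likelier in patients with a complication within each stratum. At 15% and 3 times, the retained risks are 16.9% and 6.5%, the average is 9.1%, and the difference is −0.9 points. Over the range, it runs from 1.5 to −0.9 points. Baseline adjustment restores none of it.

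**The case against.** An unadjusted comparison of two proportions is a valid and common choice under randomisation, and covariates are often left to the analysis plan. The source cited for the test is not available here, so whether that method can take strata is unknown. This stands: the plan contains no error on this point. But it does positively choose an unadjusted test as written, and it schedules the analysis plan too late for a covariate choice to be beyond question.

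Three stronger readings are tempting, and the document does not support them.

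- *A reader might infer that the plan ignores baseline risk altogether.* It does not. It replicates the primary analysis by AMG risk group, compares excluded and withdrawn participants, and runs an intention-to-treat sensitivity analysis. What is missing is an adjusted overall estimate.
- *A reader might infer that AMG is strongly prognostic for the primary outcome.* The protocol reports predictive capacity for mortality, hospitalisation, primary care use, polypharmacy and cost, not for complications of the baseline disease. Eligibility is limited to moderate complexity that needs no physical examination, which probably narrows the risk range, so c-statistics of 0.60-0.65 must be considered.
- *A reader might infer that adjustment would remove the bias created by per-protocol exclusions.* Remote participants leave when a change in clinical status requires face-to-face care (Participant timeline). That happens after randomisation and is plausibly tied to the outcome, so baseline covariates cannot repair it. One-sided examples also overstate the measured part. Suppose 30% of patients have twice the risk and 20% of them leave the remote arm only: its risk reads 0.34 points too low. If 20% have three times the risk and 30% of them leave, it reads 0.73 too low. If 10% of low-risk remote patients also leave, these shrink to 0.19 and 0.53. The control arm has its own health-linked discontinuation rule, which could offset them further.

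**Conclusion.** The point holds as a low-cost improvement to a stated method, not as an error. The primary estimate leaves out baseline risk measures that the trial already retrieves, and the stratified replications do not replace an adjusted overall estimate.

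The gain is mainly precision, and it is modest: about 1-3% of the variance at an assumed c-statistic of 0.60-0.65 and 5-15% at 0.70-0.80. It does not solve the power problem. At best the half-width falls from 2.68 to 2.48 points, so an observed difference of zero would still miss the 2-point margin.

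Adjustment removes only imbalance explained by measured baseline risk. Bias from exclusions that follow a change in clinical status remains and must be dealt with as a separate issue; an adjusted per-protocol estimate should not be read as having settled it. The sizes rest on assumed c-statistics, strata and exclusion rates, on 961 analysed per arm, and on a 10% risk.

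**What to change.** Amend Data management and analysis now, while the trial is recruiting, rather than waiting for the later analysis plan:

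1. Make the primary estimate a covariate-adjusted marginal risk difference: a logistic model with arm, AMG risk group and age, standardised over the analysed participants. Compare the upper limit of its confidence interval, at the stated 2.5% error rate, with the 2-point margin.
2. Use only values fixed before allocation. Add investigator-rated severity only if it is recorded before allocation, with a category for missing values. Prescriptions are counted at the end of the screening visit, so confirm that this precedes allocation before considering them.
3. Apply the same model to the intention-to-treat set.
4. Keep the unadjusted difference as a supportive result, and keep the replication by AMG risk group.

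The cost is amendment wording and analysis code. No new data are needed, since AMG and age come from records already being retrieved. If AMG proves weakly prognostic, little is lost. Severity is rated across unrelated diagnoses and is not a common risk scale, so it should not be relied on for the gain.

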### Interventions

Participants will be randomly allocated into one of the two study arms: control (i.e., face-to-face consultation) and remote consultation (including teleconsultation, and video consultation). All patients, irrespective of the consultation type, will receive short text message reminders a few days before the visit.

Participants allocated into the control arm will be scheduled with face-to-face appointments as usual. All phone calls (except reminders for scheduled visits) performed by the physician during the study will be noted in the electronic case report form (eCRF). Per protocol, participants allocated in the control arm can receive up to 25% of physician-doctor interactions by phone (that is, one phone call allowed for three face-to-face appointments).

Participants allocated in the remote consultation arm will be scheduled remote visits, either phone or video consultation. In case of phone visits, the physician will call the main phone number provided by the patient and, in case of not receiving an answer, other phone numbers listed as contact numbers. In case of video consultation, the participant will receive an additional text message with the visit link. When clicking the link, a website with the video consultation system embedded will open in the default browser of the user. The video consultation platform of the physician pops up a message indicating that the patient is in the virtual waiting room. Patients will remain in the virtual waiting room until the physician starts the visit. A technical assistance is readily available for physicians who experience troubles with the system. In case the patient does not show up to the video consultation after a reasonable time, the physician calls the patient by phone. The date and hour of the phone call and the reason for the inability to connect are recorded in the eCRF.

Participants allocated in the remote consultation arm that require face-to-face visits will be excluded from the per-protocol analysis, and the reason for the face-to-face visit will be recorded in the eCRF. Participants allocated in the remote consultation arm and scheduled with a phone visit cannot be visited by video, whereas those scheduled for a video consultation can undergo up to 25% of phone visits. Phone contacts and their reason in patients in the video consultation arm will be recorded in the eCRF.

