### Screening, allocation, and blinding

All consecutive patients who visited any of the participating departments between May 2022 and May 2024 will be informed about the study design and objective and will be offered to enroll in the trial. Patients who agree to participate will provide their informed consent, which will be signed in case of a face-to-face screening visit and oral in case of a remote visit. Patients who reject enrollment will be recorded in an anonymous registry. Once signed the informed consent, the investigator will assess the eligibility criteria and record them in the eCRF.

Patients will be randomly allocated in either of the study arms irrespective of the modality of the screening visit. Randomization will be balanced by medical specialty to prevent biases towards a particular diagnosis within study arms. To ensure a minimum number of participants who visited through video consultation, participants allocated to the remote consultation arm will be subsequently randomized to either video consultation or remote modality selection at physician discretion at a 3:7 ratio.

Centralized randomization will be automatically conducted by the randomization module of the REDCAP system used for the eCRF. The allocation will be informed to the administrative service, which will schedule all visits indicated by the physician during the investigated period following the criteria of each study arm. The health condition for which a patient has attended the screening visit will be considered the baseline disease for the study purposes.

Although study participants will be informed about the overall study objectives in the patient information sheet, they will not be aware of the study endpoints. In addition, the statisticians performing the analysis will be blinded to participant allocation. No rules for unblinding have been pre-defined in the study protocol.

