The users’ satisfaction with the quality of care received will be assessed using a validated tool encompassed within the satisfaction survey plan of the Catalan Health Service [22]. The questionnaire consists of 32 items that combine binary and multiple choice questions, 10-point assessment scales, and 2 open questions. An interview panel will administer the questionnaire by phone to a subset of 300 participants (100 per arm), randomly selected from all participants who have completed the final visit.

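### The primary test is described as one for a three-arm trial, but the randomisation, the primary contrast and the sample size are all two-group, and no teleconsultation arm is randomised

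*Protocol article*

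**What the plan says.** **Allocation.** Under Interventions, participants are "randomly allocated into one of the two study arms: control (i.e., face-to-face consultation) and remote consultation". Under Screening, allocation, and blinding, those in the remote arm are "subsequently randomized to either video consultation or remote modality selection at physician discretion at a 3:7 ratio". The stated purpose of this second step is to secure a minimum number of video participants.

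**Primary contrast.** Under Data management and analysis, the cumulative incidence of complications is compared "between remote consultation (video and teleconsultation arms) and face-to-face consultation, using a non-inferiority margin of 2" per cent. The per-protocol set is primary and intention-to-treat is a sensitivity analysis.

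**Primary test.** The same paragraph names a "modified binomial test to assess the non-inferiority of an experimental intervention vs. a control group in a three-arm trial", with a literature citation.

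**Sample size.** Sample size considerations uses one face-to-face rate (10%) and one remote rate (12%), and arrives at 1068 per arm and 2136 in total.

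**Other uses of the word arm.** The satisfaction survey (Outcomes and variables) interviews "a subset of 300 participants (100 per arm"), which implies three arms. Participant timeline speaks of remote arms in the plural. Interventions mentions a video arm and treats phone or video as something to which a patient has been allocated.

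**The concern.** The test that decides the trial is described for a design that this trial does not have. The two modality arms in the analysis paragraph are also not groups formed by randomisation: video is assigned to three in ten remote patients, and for the other seven in ten the physician picks phone or video.

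Two statisticians could therefore follow the same paragraph and do different things. One would compare all remote patients with all face-to-face patients. The other would run a three-group procedure, either on the allocation groups or on the modality received. Only the first matches the stated contrast and the sample size. In the last, patients are sorted into phone and video partly by the physician's judgement, which may depend on their expected risk of complications. The groups would then no longer be comparable by design.

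**Working it through.** **1. Which design does the sample size assume?** Inputs from Sample size considerations: face-to-face rate 0.10, remote rate 0.12, margin 0.02 (taken as an absolute difference), type I error 2.5% (taken as one-sided), power 80%, loss 10%.

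Two-sample non-inferiority formula, unpooled variance, 1:1:

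n = [p₁(1 − p₁) + p₂(1 − p₂)] × (z₀.₉₇₅ + z₀.₈₀)² / d²

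- Variance term: 0.10 × 0.90 + 0.12 × 0.88 = 0.1956.
- (1.960 + 0.842)² ≈ 7.85.
- Distance d = 0.04. The stated figure is reproduced only if the expected 2-point difference is added to the margin.
- n = 0.1956 × 7.85 / 0.0016 ≈ 959.5, so 960 per arm.
- After 10% loss: 960 / 0.90 = 1066.7, so 1067 per arm and 2134 in total. The article states 1068 and 2136.

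The stated size is thus a two-group calculation to within one patient per arm. Adding the difference to the margin treats a higher complication rate as favourable. That is a separate problem and does not affect this point; the formula serves here only to identify the design behind the figure.

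**2. Which groups does the randomisation create?** In a remote arm of 1068:

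- assigned to video: 0.3 × 1068 ≈ 320;
- modality chosen by the physician: 0.7 × 1068 ≈ 748;
- assigned to phone: 0.

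The number followed by phone could lie anywhere from 0 to about 748, depending on physicians' choices. Interventions also lets patients scheduled for video have up to 25% of their visits by phone, so the modality received differs further from the modality assigned.

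**3. The elements side by side.**

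| Element | Groups |
|---|---|
| Main randomisation | Two: face-to-face, remote |
| Primary contrast and margin | Two: pooled remote v face-to-face, one margin |
| Sample size | Two: 2 × 1068 = 2136 |
| Second-stage randomisation | Splits remote into video-assigned and physician's choice |
| Named primary test | Described for three arms |
| Arms named in the analysis paragraph | Video, teleconsultation, face-to-face |
| Satisfaction survey | Three: 300 / 100 |

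The last three rows do not fit the first three. The fourth row gives three allocation groups, but they are not the video and teleconsultation arms of the analysis paragraph.

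**The case against.** The strongest reply is that the primary question is defined. The article gives one contrast and one margin, and the quoted phrase itself describes an experimental intervention against a control, which is pairwise. The second-stage randomisation does produce three allocation groups, which may explain the wording. Nothing in the analysis paragraph says that phone and video will be contrasted with each other, and the survey subsample concerns a secondary outcome. All of this stands. It limits the finding to the named test and the wording about arms, but does not remove it: no phone group is randomised, and the text does not say how a three-arm procedure would be applied to a two-group contrast.

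A reader might infer more than the documents support:

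- **That type I error, or the meaning of non-inferior, is undefined.** This would require knowing the null hypothesis and variance of the cited method, which is not available. It may reduce to a two-sample comparison.
- **That power is about 17%.** With both rates assumed to be 10%, video-assigned against face-to-face (288 v 961 evaluable) has SE = √(0.09/288 + 0.09/961) = 0.0202 and power Φ(0.02/0.0202 − 1.96) ≈ 0.17. The protocol does not make this comparison primary. On the same assumption the pooled contrast (961 v 961) has only about 31%, so much of the shortfall comes from the sample size and margin.
- **That 3 × 1068 = 3204 patients are needed.** The protocol plans 2136 and states no three-arm hypothesis.
- **That the timing of the statistical analysis plan worsens the error.** The plan "will be performed after the last patient has attended the final visit and before the closure of the database", and the statisticians are to be blinded. Whether that is early enough is a separate question from whether the test fits.

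**Conclusion.** The point holds as an internal mismatch in a stated primary analysis; it is not a detail left to a later document. The named test, as the article describes it, agrees with neither the randomisation, the pooled contrast nor the two-group sample size, and the phone and video arms it appears to rely on are not randomised groups.

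The contrast, the margin and the planned number are all stated, and correcting the test changes none of them. No effect on type I error or bias has been calculated, and none can be without the cited method. Confounding by physician choice is conditional: it arises only if the groups are formed by modality received.

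The conclusion rests on the article's own description of the test, and on reading the margin as absolute and the 2.5% as one-sided. It does not imply that the sample size is adequate.

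**What to change.** In Data management and analysis, replace the named test with a two-sample non-inferiority test of the risk difference, pooled remote against face-to-face by allocated arm, for example Farrington–Manning or Miettinen–Nurminen. Claim non-inferiority if the upper limit of the one-sided 97.5% confidence interval for remote minus face-to-face is below 2 percentage points. Apply it in the sets the protocol already states: per-protocol as primary and intention-to-treat as sensitivity.

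Report any video comparison descriptively by randomised sub-allocation (video-assigned, physician's choice, face-to-face), and do not present phone against video by modality received as a randomised contrast.

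Align the wording about arms in Data management and analysis, Participant timeline and the satisfaction paragraph of Outcomes and variables. For the survey, say which three groups are sampled.

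The cost is an amendment to the wording. It needs no further patients or data, the planned number stays as it is, and the article reports that recruitment was still under way.
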